## Design and Methods

This double-blind randomised cross-over clinical trial consists of two arms. Severity of the gait disturbance will be assessed after a three week follow-up of both *(i) *conventional stimulation of the STN area [STNmono] and *(ii) *combined stimulation of the STN area and the caudal STN/SNr border zone [STN+SNr]. 12 consecutive patients will be randomised on blocks to the two treatment conditions in a 1:1 ratio and treatments will be crossed-over after three weeks of follow-up, respectively. Moreover, a baseline assessment *'off dopaminergic medication' *will be performed in order to assess short-term effects and to assure optimal stimulation parameters of the conventional STN-DBS [STNmono]. A composite 'axial score' including the major clinical and anamnestic items on gait, posture and balance function from UPDRSII (items 13-15) and UPDRS III (items 27-31) constitutes the primary outcome measure.

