### Study protocol

Clinical testings at baseline will be performed after overnight withdrawal of dopaminergic medication and after optimization of subthalamic stimulation. Follow-up examinations will be performed in the *'dopaminergic on state'*. Of note, no follow-up examinations with a single active SNr contact will be conducted as this previously failed to control for segmental symptoms like tremor, bradykinesia and rigidity [17].

Figure 1: Baseline testings will be performed *"off dopaminergic medication" *after overnight withdrawal with *(i) *[StimOff], *(ii) *[STNmono], and *(iii) *[STN+SNr]. On visits 1 and 2, we will assess the treatment effects of [STNmono] and [STN+SNr] after three weeks of constant stimulation on either setting. The order of the treatment conditions will be randomized and crossed after the first visit. Randomisation lists for the different treatment conditions are prepared by the Department of Medical Biometry.

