### Sample size calculation and statistical analysis plan

#### Primary Endpoint

The primary endpoint for the statistical evaluation of the therapy is the change in composite 'axial score'. The 'axial score' is built by 8 items from the UPDRS II and III, all 5-point rated. For the statistical evaluation the five rating points are represented by the numbers 0 to 4, which represent increasing levels of pathology. The 'axial score' will be scored by the sum of the ratings across the 8 items (range 0 to 32). As change in UPDRS scores is a common primary efficacy outcome measure in Parkinson's disease and only items of the original UPDRS are required for the definition of the primary endpoint the statistical evaluation methods should be based on the psychometric validation of the UPDRS and no own validation studies are necessary.

The primary endpoint for the statistical evaluation will be the change in 'axial score' from baseline to visit 2 (after 6 weeks). For every patient we will determine two change-scores for the two phases in the Cross-Over. By means of a paired t-test the null hypothesis of equality of the two therapies concerning the change in 'axial score' will be tested. The decision for maintaining or rejecting the null hypothesis will be made applying a two-sided test with α = 0.05. The observed effects will be described by use of means and effect sizes including the appropriate 95%-confidence intervals. The confirmatory statistical evaluation of the efficacy of the [STN+SNr-DBS] in this trial will be restricted to the primary endpoint. Only the rejection of the null hypothesis will be interpreted as statistical evidence for the efficacy of [STN+SNr-DBS].

As no comparable study is available at the moment, we defined an improvement of 4 points on the primary outcome measure 'axial score' to be clinically relevant on hypokinetic gait disturbances and assumed a standard deviation of 4.0 (effect size: 1.0). A sample size of 10 will have 80% power to detect a difference in means of 4.0 (e.g. first condition mean: 16.0 and a second condition mean of 12.0), using a paired t-test with a 0.05 two-sided significance level (sample size estimated using NQuery Advisor 7.0). To adjust for a maximum of two dropouts a total of n = 12 patients will be included in the study.

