#### Handling of Missing Data

All variables included in the CRF are mandatory. The monitoring will assure quality of the assessments. Thus, missing values are to be expected (eg. refusal of patients). Patients with missing values for the primary endpoint will be included with the last observed score before the planned time point (last-observation-carried-forward). All randomised patients will be included (Intention-to-treat).

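### The only confirmatory test is a paired t-test with no period term, so any period effect in this block-randomised cross-over is counted as noise and costs power

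*Protocol article*

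**What the plan says.** The Design and Methods section describes a 2 × 2 cross-over: "12 consecutive patients will be randomised on blocks to the two treatment conditions in a 1:1 ratio". The Study protocol section makes clear that what is randomised is the sequence: "The order of the treatment conditions will be randomized and crossed after the first visit".

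The Primary Endpoint section forms two change-scores per patient and fixes the test: "By means of a paired t-test the null hypothesis of equality of the two therapies concerning the change in 'axial score' will be tested", "applying a two-sided test with α = 0.05". It adds that only rejection by this test will count as statistical evidence of efficacy. On size it says: "A sample size of 10 will have 80% power to detect a difference in means of 4.0", with an assumed SD of 4.0, and then: "To adjust for a maximum of two dropouts a total of n = 12 patients will be included in the study".

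The Handling of Missing Data section keeps all randomised patients in the analysis: "Patients with missing values for the primary endpoint will be included with the last observed score before the planned time point".

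The Treatment section argues that three weeks on each setting is long enough to deal with carry-over. It does not discuss a period effect, and no period or sequence term is named anywhere. The Discussion says that a larger efficacy study will be designed from the effect size and SD found here.

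**The concern.** Carry-over and period effects are separate matters. That stimulation effects fade within seconds to hours speaks to carry-over. It does not exclude a general shift between visits 1 and 2 from expectation, repeated testing or self-report (three of the eight items come from UPDRS II and are anamnestic).

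Such a shift adds to the treatment difference in one sequence and subtracts from it in the other. Randomising the order in balanced blocks is what allows it to be separated out. The paired t-test pools the two sequences as one sample and leaves the shift in the error term. At stake are the power of a 12-patient trial with one confirmatory test, the width of its promised confidence interval, and the SD handed on to the next study.

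**Working it through.** **Inputs from the article.** Difference 4.0; SD 4.0, which with effect size 1.0 in a paired test is the SD of the within-patient difference; two-sided α = 0.05; 12 randomised 1:1; 10 evaluable.

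**Assumptions.** The article gives no period effect. Let π be the visit 2 minus visit 1 shift under the same treatment, varied from 0 to 3 points. Both change-scores are taken to share one baseline, which then cancels from their difference.

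**Step 1: the plan's own figure.** Paired t-test, n = 10: noncentrality 4/(4/√10) = 3.16, df = 9. Power is 80.3% (74.8% at n = 9). The stated sample size reproduces. At n = 12 power is 88.3%.

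**Step 2: mechanism.** Let D be the score on [STN+SNr] minus the score on [STNmono], with true mean τ and error e of SD 4.
- [STN+SNr] second: D = τ + π + e
- [STN+SNr] first: D = τ − π + e

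With equal sequences the mean of D is τ, so there is no bias. The SD that the paired t-test uses becomes √(16 + π²·n/(n−1)). For π = 2 and n = 12 this is √(16 + 4 × 12/11) = √20.36 = 4.51.

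**Step 3: size.** Simulation with a true difference of 4 points. The adjusted test averages the two sequence means and uses the pooled within-sequence variance with n − 2 df.

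| π (assumed) | SD used, 6:6 | Paired power, 6:6 | Adjusted, 6:6 | Paired power, 5:5 | Adjusted, 5:5 | True α of paired test |
|---|---|---|---|---|---|---|
| 0 | 4.00 | 88% | 88% | 80% | 79% | 5% |
| 1 | 4.13 | 87% | 88% | 78% | 79% | about 4.3% |
| 2 | 4.51 | 82% | 88% | 72% | 79% | about 3.0% |
| 3 | 5.08 | 74% | 88% | 62% | 79% | about 1.6% |

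**Step 4: effect size passed on.** At 6:6 a true effect size of 4/4 = 1.0 would appear as about 4/4.51 = 0.89 for π = 2 and 4/5.08 = 0.79 for π = 3.

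**Step 5: dropouts under the stated rule.** A patient who misses visit 2 has the visit 1 score carried forward, so D = 0. Take two such patients in the sequence with [STN+SNr] first.
- Paired mean: [6(τ + π) + 4(τ − π) + 0]/12 = (10τ + 2π)/12
- Average of sequence means: [(τ + π) + (4/6)(τ − π)]/2 = (10τ + 2π)/12

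The two estimates are identical. With τ = −4 and π = 2 both are −36/12 = −3.0. With the two dropouts in the other sequence both are −44/12 = −3.67. With π = 0 both are −40/12 = −3.33. The distortion comes from last-observation-carried-forward (LOCF), and a period term applied to carried-forward values does not remove it.

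**Step 6: cost with no period effect.** Adjusted against paired power: 87.6% against 88.3% at 6:6, 79.1% against 80.3% at 5:5, and 77.4% against 80.3% at 6:4.

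**The case against.** The strongest reply is that the period effect is hypothetical. Medication is constant for the six weeks and stable for four weeks before; disease duration is at least 5 years and implantation at least 6 months past; settings are switched several times before one is kept. A 3-point shift would be three quarters of the 4-point relevant difference. At 1 point the loss at 6:6 is about 1 point of power, and at 0 the paired test is slightly better. All of this stands. It makes the size conditional but does not show the effect to be nil, and the article does not argue that it is.

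A second reply is that a conservative test cannot mislead: if it rejects, the rejection is valid. That also stands for balanced sequences. The harm there is lost power and too wide an interval, not false positives.

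A reader might infer that dropouts will unbalance the sequences and so bias the planned estimate, for example by π × (6 − 4)/10 = 0.4 points at 6:4 with π = 2. The article does not support this as the main point. A 6:4 split describes a completer analysis, whereas the stated rule keeps all 12 patients. The power comparison at 6:4 also runs both ways: with a 2-point shift the paired test has about 63% against 77% adjusted in one direction, and 81% against 77% in the other.

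Finally, the sample size was computed for the paired t-test, so the change is not wording alone; the power statement must follow.

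**Conclusion.** The point holds as one of efficiency. The article itself fixes an unadjusted paired t-test as the sole confirmatory analysis of a sequence-randomised cross-over, so this is not a detail left to a fuller plan. With balanced sequences the estimate is unbiased and the type I error is at or below 5%. The loss is slight up to about 1 point of period effect and material from about 2 points: 6 points of power at 6:6 and 7 at 5:5, rising to 14 and 17 at 3 points. These figures rest on the article's difference and SD of 4.0 and on an assumed period effect. The inflated SD would also lower the effect size from which the next study is to be designed.

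Bias from dropouts is a separate matter that arises from LOCF, and neither test cures it on carried-forward data.

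**What to change.** Make the primary analysis period-adjusted, in one of two forms:
- a two-sample t-test comparing the within-patient period differences between the two sequences, with the treatment effect estimated as the average of the two sequence means; or
- a mixed model with fixed treatment and period and random patient.

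The two agree only when every patient has both visits. The mixed model fitted to observed scores, and not to LOCF values, is preferable because it also deals with the period bias that dropouts bring. Keep the paired t-test as a sensitivity analysis.

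Restate the power for the adjusted test: about 79% with 10 balanced completers, just under the 80% target, and about 88% with 12.

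The cost is one degree of freedom and revised text for the analysis and sample size, with no extra patients or data. If there is no period effect, power falls by under 1 point at 6:6, about 1 point at 5:5 and about 3 points at 6:4.

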#### Secondary Endpoints

As all secondary endpoints are based on validated scores, we assume that parametric statistical methods can be used for the analysis. The secondary endpoints will be compared and statistically assessed for descriptive purposes and not in a confirmatory sense. The aim is explorative data analysis, not hypothesis testing or generation of evidence for efficacy. Because of the explorative character of this part of the analysis, no a priori statistical analysis plan exists. If adequate, changes of scores over time will be analysed with paired t-tests or appropriate statistical methods (eg. Repeated Measurements Anova). If a categorization of scores should be adequate (eg. classification in success vs. failure according to score-cut-offs) we will use adequate analysis methods for categorical variables (eg. McNemar Test). In addition, appropriate statistical methods of explorative data analysis including graphical methods and descriptive statistics will be used. No interim analysis and no subgroup analysis are planned.

#### Handling of Missing Data

All variables included in the CRF are mandatory. The monitoring will assure quality of the assessments. Thus, missing values are to be expected (eg. refusal of patients). Patients with missing values for the primary endpoint will be included with the last observed score before the planned time point (last-observation-carried-forward). All randomised patients will be included (Intention-to-treat).

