After the baseline examination, patients will be randomised to either [STNmono] or [STN+SNr] treatment and scheduled at three weeks of constant stimulation (Visit 1). After this first endpoint assessment treatment will be crossed-over and patients will be re-scheduled after further three weeks of constant stimulation for the second endpoint assessment (Visit 2). The follow-up period is - due to the current clinical evidence - sufficiently long to control adequately for carry-over effects since the endpoint assessment in the follow-up period will be scheduled only after three weeks of constant stimulation on either setting. STN-DBS in PD generally evokes clinical effects within short time intervals ranging from several seconds to few hours and presents completely reversible in the same time range. In the first patient described with improvement from [STN+SNr] compared to [STNmono], the clinical superiority of [STN+SNr] was demonstrated after 30 minutes of constant stimulation on either setting [18], and monopolar stimulation on STN or SNr contacts revealed discriminable clinical effects on segmental and axial symptoms if both settings were applied randomly within one day in an independent study [17]. Dopaminergic medication will be held constant during the whole six week cross-over period and should be stable for at least 4 weeks before study enrolment.

Importantly, we did not consider stimulation on a single monopolar contact in the SNr area in our study design as this failed to improve segmental symptoms previously [17], and therefore is not applicable for adequate management of Parkinsonian motor symptoms.

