## Discussion

The treatment of hypokinetic gait disturbances refractory to dopaminergic medication and conventional STN-DBS constitutes an unmet therapeutic need with important impact on quality of life. Current concepts aim on neuromodulation of reciprocal functional locomotor circuitries of basal ganglia and brainstem that hold an integrative key role within the locomotor system. This double-blind controlled cross-over phase II clinical trial has been designed to evaluate both short-term and long-term efficacy of a novel stimulation paradigm using '*interleaved pulses' *on subthalamic and nigral electrode contacts for refractory gait disturbances. Based on the effect size and standard deviation of the Intention-to-treat analysis a larger clinical efficacy study will be designed.

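### Carrying the last score forward fills a missing Visit 2 with the score from the other stimulation setting and biases the estimated treatment difference towards zero

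*Protocol article*

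**What the plan says.** The section Handling of Missing Data sets the rule for the primary endpoint: "Patients with missing values for the primary endpoint will be included with the last observed score before the planned time point (last-observation-carried-forward". It keeps every randomised patient in the analysis ("All randomised patients will be included (Intention-to-treat") and anticipates gaps ("Thus, missing values are to be expected (eg. refusal of patients"). It makes no exception for the cross-over.

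The Treatment section gives one endpoint assessment per period. In period 1, "patients will be randomised to either [STNmono] or [STN+SNr] treatment and scheduled at three weeks of constant stimulation (Visit 1". Then, "After this first endpoint assessment treatment will be crossed-over and patients will be re-scheduled after further three weeks of constant stimulation". The Study protocol section adds that "Clinical testings at baseline will be performed after overnight withdrawal of dopaminergic medication", whereas both follow-up visits take place on medication.

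The Primary Endpoint section compares two change scores per patient, one per phase, with a paired t-test. It does not say whether both are measured from the same baseline. The Discussion says what the result is for: "Based on the effect size and standard deviation of the Intention-to-treat analysis a larger clinical efficacy study will be designed".

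**The concern.** Carrying a score forward presumes that the earlier value was taken under the same treatment as the missing one. Here it never was. The score before Visit 2 is Visit 1, under the opposite setting. The score before Visit 1 is the baseline, which was taken off medication after short-term testing of three stimulation conditions. The rule does not say which of the three is carried.

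The imputed value therefore carries no information about the setting it stands in for, yet it enters the confirmatory test as a full patient. With 12 patients, each one is 1/12, or about 8%, of the mean. At stake is the estimated benefit and its standard deviation, the two quantities on which the next trial is to be sized.

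**Working it through.** **Inputs.** From the Primary Endpoint section: benefit 4.0 points, SD 4.0, two-sided alpha 0.05, 10 evaluable patients, 12 enrolled to allow for two dropouts. Benefit D is the axial score on STNmono minus the score on STN+SNr, so positive values favour STN+SNr. SD 4.0 is read as the SD of the within-patient differences.

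**The plan's own figure.** Paired t-test, df = n - 1, noncentrality = √n × 4/4. For n = 10 this is √10 = 3.16 with 9 df, and exact power is 80.3%. For n = 9 it is 74.8% and for n = 12 it is 88.3%. The stated 10 patients and 80% are reproduced.

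**Visit 2 missing (V2 := V1).** Let B be the baseline score.
- Common baseline: the change scores are V1 - B and V1 - B, so the difference is exactly 0. The same happens if both visits are missing, because both then carry B.
- Phase-2 change taken from Visit 1 instead: that change is 0, and the paired difference becomes V1 - B, the phase-1 change from an off-medication baseline. This is not a treatment contrast either.

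**Size with a common baseline.** The means are arithmetic. SD and power come from 200,000 simulated trials with D ~ N(4, 4).

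| Case | Expected benefit | Mean SD | Power |
|---|---|---|---|
| 12 complete | 4.00 | 3.91 | 88.3% |
| 10 completers, no imputation | 4.00 | 3.89 | 80.3% |
| 1 of 12 set to 0 | 11 × 4/12 = 3.67 (-8.3%) | 3.91 | 84.6% |
| 2 of 12 set to 0 | 10 × 4/12 = 3.33 (-16.7%) | 3.89 | 79.8% |

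With two zeros the effect size is 3.33/3.89 = 0.86. The planning value is 1.0, and 12 complete patients give 4.00/3.91 = 1.02 on the same scale. Averaging the effect size trial by trial gives 0.88 with two zeros and 1.10 in 10 completers. With no true effect and two zeros, type I error is 4.8%. A next trial sized on 0.86 rather than 1.0 would be about (1/0.86)² = 1.35 times as large.

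**Visit 1 missed, Visit 2 attended.** V1 takes an off-medication baseline score while V2 is on medication. The off/on gap g is not given in the article, so 4, 8 and 12 points are assumed, with the STNmono baseline carried:
- Two patients due STNmono first, each with expected difference 4 + g: mean = 4 + 2g/12 = 4.67, 5.33, 6.00.
- Two patients due STN+SNr first, each with difference -g: mean = (40 - 2g)/12 = 2.67, 2.00, 1.33.
- One of each: mean = (40 + 4 + g - g)/12 = 3.67, whatever the gap.

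The answer also depends on which baseline condition is carried. Take a 6-point gap and two patients due STN+SNr first. Power is 54% if the matching condition is carried and 12% if the STNmono score is. Such figures are illustrations only.

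**Dropout because of worsening.** Suppose 11 patients have benefit 4 and one is truly 6 points worse on STN+SNr and leaves in period 2 (illustrative figures).
- True mean: (44 - 6)/12 = 3.17.
- Last score carried forward: 44/12 = 3.67, a bias of 0.50 in favour of STN+SNr.
- Observed data only: about 4.00 if that patient's Visit 1 is typical, a bias of 0.83.

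Deleting the rule therefore does not by itself deal with this patient.

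**The case against.** The best defence is that the realistic case is mild. With at most two Visit 2 dropouts, power is within half a percentage point of the planned figure and type I error stays at or below 5%. If missingness is unrelated to outcome, the bias is towards no difference, so a positive result would not be manufactured. This stands, and it rules out the claim that the confirmatory test is broken.

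Three stronger readings are tempting, and the document does not support them.

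- **The drug effect routinely contaminates the result.** That needs a patient who misses Visit 1 but attends Visit 2. The switch is tied to Visit 1, and a withdrawn patient leaves the study at once, so ordinary dropout before Visit 1 leaves both visits missing and gives a zero with a common baseline. Large losses or gains in power also need two such patients in the same sequence, an assumed gap and a chosen baseline condition.
- **The zero is unconditional.** It requires a common baseline, which the Primary Endpoint section does not state. The alternative reading is also invalid, but in another way.
- **The rule hides harm.** A patient who worsens in period 2 and leaves does count as no difference in the efficacy mean. But the Safety section makes severe worsening of gait a separate endpoint recorded in the CRF, so it is not lost from the trial's record.

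It is also fair to say that a mixed model alone is no cure for dropout caused by worsening, as the last calculation shows. This is why the fix has a second part.

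**Conclusion.** The rule is wrong as written and should be fixed. Each setting has a single endpoint visit, so a score carried forward into Visit 2 always comes from the other setting. At the dropout the plan allows for, with both patients missing Visit 2 and a common baseline, the expected benefit is diluted by 17% (4.0 to 3.33) and the effect size falls to about 0.86. This assumes the plan's own benefit and SD, and missingness unrelated to outcome. The damage is to the estimate and to the next trial built on it. Power and type I error are almost untouched in this case. The off-medication comparison after a missed Visit 1 is a real defect of the rule, but its size cannot be fixed from the document.

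**What to change.** Delete the last-observation rule. Base the primary analysis on the observed on-medication Visit 1 and Visit 2 axial scores of all randomised patients, in a mixed model with treatment and period as fixed effects and patient as a random effect. With few dropouts this is close to analysing complete pairs. It also avoids having to choose a baseline for the change scores.

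Add one pre-specified sensitivity analysis: any patient who stops a setting because of worsening receives a defined unfavourable value for that setting, for example the worst score observed in it. This part is needed because the mixed model does not correct for such dropout.

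The cost is a change of wording and a few lines of code. A patient seen in only one period contributes less than under the present rule, so the confidence interval may be slightly wider. No visit or design feature changes.
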